48    BCVA = best-corrected visual acuity;

49    CCT = central corneal thickness;

50    D = diopter;

51    IOP = intraocular pressure

52    UCVA = uncorrected visual acuity;

53    OCT = optical coherence tomography;

54    RCT = randomized controlled trial;

55    RLRL = repeated low-level red-light;

56    RPE = retinal pigment epithelial;

57    SAE = serious adverse event

58    SFCT = subfoveal choroidal thickness;

59    SER = spherical equivalent refraction;

60

61

62

63    **1. Trial information**

64    **1.1 Title of project**

65    the efficacy and safety in children following 650 nm red-light therapy for myopia control

66

67    **1.2 Trial summary**

68    **Objective:** To observe the effect of low-intensity 650 nm red light on the prevention of  
69                   myopia in adolescents, whether it can effectively curb myopia or slow down the  
70                   development of myopia in children at high risk of myopia. we hope to provide  
71                   new methods and ideas for effectively controlling myopia.

72    **Trial Setting:** The randomized controlled clinical trial is planned to be conducted between  
73                   September 2021 and September 2023 at the Eye Center of the Children's  
74                   hospital of Fudan University, China

75    **Sample size:** A sample size of 86 (43 in each group) is estimated after adjusting for a 20% loss  
76                   to follow-up.

77    **Inclusion criteria:** 1) Children aged 7-12 years old.

78                   2) Children with pre-myopia or mild myopia.

79    **Exclusion criteria:** 1) Participated in any myopia control clinical research trial within 3 months,  
80                   used or is currently using multifocal contact lenses, atropine drugs, etc.;

81                   2) Children with strabismus and amblyopia;

82                   3) Congenital eye diseases, such as congenital cataracts and congenital  
83                   retinal diseases;

84                   4) Secondary myopia (such as secondary myopia caused by retinopathy of  
85                   prematurity or other infant eye diseases), or myopia combined with  
86                   systemic syndromes (such as Marfan syndrome);

87                   5) People who have undergone myopia correction (such as LASIK, etc.),  
88                   internal eye surgery (such as cataract extraction, intraocular lens  
89                   implantation, etc.);

90                   6) refractive media turbidity (such as keratopathy, crystal turbidity, etc.)

91                   7) Abnormal IOP (IOP < 10 mmHg or > 21mmHg or binocular IOP  
92                   asymmetry  $\geq 5$ mmHg);

93 8) Patients with fundus retinopathy or other intraocular diseases;  
94 9) Patients with optic nerve damage or congenital optic nerve dysfunction;  
95 10) Have systemic diseases that may affect the eyes, such as diabetes,  
96 Down syndrome, hyperthyroidism, etc;  
97 11) Only one eye meets the inclusion criteria;  
98 12) Those who cannot regularly (or the guardian cannot regularly  
99 accompany the children) carry out eye examination;  
100 13) Other reasons that the doctor considers unsuitable for inclusion in the  
101 program.

102 **Interventions:** Eligible patients will be randomly allocated with a ratio of Interventions 1:1  
103 into 2 groups.

104 **Follow-up plan:** Each patient will undergo examinations at 1 month, 3months, 6 months, 9  
105 months and 12 months after the enrollment.

106 **Primary outcome:** The change in axial length (AL).

107 **Secondary outcome:** The changes of uncorrected distance visual acuity (UCVA), best-  
108 corrected visual acuity (BCVA), spherical equivalent refraction (SER),  
109 subfoveal choroidal thickness (SFCT), and central cornea thickness  
110 (CCT).

111

## 112 2. Background

113 Myopia represents one of the most common eye conditions worldwide, with a rapid  
114 increasing prevalence and an earlier age of onset. It is estimated that approximately 4.758  
115 billion people will be affected by myopia, and 938 million people will have high myopia by  
116 the year 2050. Previous studies conducted on 6- to 7-year-old children have shown that the  
117 prevalence of myopia was as high as 39.5% in Guangzhou and rang from 20% to 30% in  
118 Taiwan. The early onset of myopia has been demonstrated to increase the risk of developing  
119 high myopia. To date, various clinical interventions for myopic controlling, including  
120 orthokeratology lens, multifocal soft contact lenses, and atropine, have been explored.  
121 However, the overall efficiency in controlling myopia has ranged from 30% to 60%.

122 Recently, repeated low-level red-light (RLRL) therapy has gained significant attention as an  
123 alternative to outdoor light exposure in the treatment of myopia. A multi-center randomized  
124 controlled clinical trial of repeated low-level red-light (RLRL) irradiation for myopia control in  
125 school-age children was conducted in China from 2019 to 2020, providing evidence of the  
126 effectiveness, safety, and subject compliance of this technology in adjuvant myopic control.

127 However, there are currently few relevant studies, and more data support is still needed,  
128 especially for children in the pre-myopia stag. Our study aims to assess the efficacy of RLRL  
129 therapy for myopia control at an early stage.

130

## 131 3. Study design

132 The study will be a 1-year, single-center, randomized, and placebo-controlled trial, with a 1:1  
133 allocation to intervention group (RLRL treatment) or control group (observe or wear single  
134 vision glasses).

135

### 136 3.1 Scheme

[figure not shown]

137

138

## 139 3.2 Participants

### 140 3.2.1 Inclusion criteria

141 1) Children aged 7-12 years old.

142 2) Children with pre-myopia or mild myopia.

### 143 3.2.2 Exclusion criteria

144 1) Participated in any myopia control clinical research trial within 3 months, used or is currently  
145 using multifocal contact lenses, atropine drugs, etc.;

146 2) Children with strabismus and amblyopia;

147 3) Congenital eye diseases, such as congenital cataracts and congenital retinal diseases;

148 4) Secondary myopia (such as secondary myopia caused by retinopathy of prematurity or  
149 other infant eye diseases), or myopia combined with systemic syndromes (such as Marfan  
150 syndrome);

151 5) People who have undergone myopia correction (such as LASIK, etc.), internal eye surgery  
152 (such as cataract extraction, intraocular lens implantation, etc.);

153 6) refractive media turbidity (such as keratopathy, crystal turbidity, etc.)

- 154 7) Abnormal IOP (IOP < 10 mmHg or > 21mmHg or binocular IOP asymmetry  $\geq$ 5mmHg);  
155 8) Patients with fundus retinopathy or other intraocular diseases;  
156 9) Patients with optic nerve damage or congenital optic nerve dysfunction;  
157 10) Have systemic diseases that may affect the eyes, such as diabetes, Down syndrome,  
158 hyperthyroidism, etc;  
159 11) Only one eye meets the inclusion criteria;  
160 12) Those who cannot regularly (or the guardian cannot regularly accompany the children)  
161 carry out eye examination;  
162 13) Other reasons that the doctor considers unsuitable for inclusion in the program.

### 163 **3.2.3 Sample size**

164 The sample size estimation was estimated based on the assumption of a 2-sided  $\alpha$  level of  
165 0.05, 90% power. The axial elongation among Chinese children with premyopia or mild myopia  
166 was approximately 0.40 mm per year (standard deviation [SD]: 0.25 mm) according to the  
167 literature. A 50% treatment effect was expected (reducing axial elongation by 0.20 mm). The  
168 sample size was required 34 per group. A total of at least 85 participants was obtained after  
169 adjusting for a 20% loss to follow-up. The sample size was calculated using PASS 15.0 (NCSS,  
170 Utah).

171

### 172 **3.3 Randomization**

173 Eligible participants will be randomized to the RLRL group or the control group. A computer-  
174 based random number table was generated with an allocation ratio of 1:1. The subjects and  
175 the clinicians were not masked to the interventions. Other investigators, and the statistician  
176 will be masked to study allocation.

177

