## 202 **3.5 Outcomes**

### 203 **3.5.1 Primary outcome**

204 The primary outcome is AL change from baseline at 1 year between the two groups.

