### 205 **3.5.2 Second outcomes**

206 1) the changes of UCVA and BCVA

207 2) the changes of SER, SFCT and CCT

208 3) the changes in the myopia incidence rate between the two groups.

209

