#### 241 **5. Statistical Analyses**

242 For each subject, data from the right eyes were utilized for analyses. Missing data were not  
243 imputed or replaced. The changes in ocular parameters were calculated as a difference  
244 between baseline and the respective follow-up values.

245 Statistical analysis includes statistical descriptions and statistical inference. Continuous  
246 variables were presented as means and standard deviations, while categorical data were  
247 presented by frequency and percentage. Group differences between the RLRL and control  
248 groups were assessed using t-test or ANOVA for continuous data and the Chi-square test for  
249 categorical data. Statistical significance was set at two-sided  $P < 0.05$ , and all analyses were  
250 performed using SPSS software version 21.0 (IBM., Chicago, IL).  
251

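### Allocation and the stated AL comparison both ignore baseline refractive status; the comparison stays valid, but a cheap gain in precision and robustness is given up

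*Protocol*

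**What the plan says.** Protocol Section 3.2.1 admits "Children with pre-myopia or mild myopia", with no target share of either type. Section 3.3 gives the allocation method in one sentence, a computer-"based random number table was generated with an allocation ratio of 1:1. The subjects and" (the last three words open the next sentence, on masking). No stratum, block or minimization factor is named there or elsewhere.

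Section 3.5.1 fixes the endpoint: "The primary outcome is AL change from baseline at 1 year between the two groups". Section 5 fixes the comparison: "groups were assessed using t-test or ANOVA for continuous data and the Chi-square test for" categorical data. It names no baseline covariate. The visit schedule in Section 3.6.1 has cycloplegic refraction at baseline, so the variable needed for stratification or adjustment is already collected.

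Section 3.2.3 plans on a single elongation figure for both types together, 0.40 mm per year with SD 0.25 mm, and an effect of 0.20 mm.

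**The concern.** Refractive status at entry is the most visible way in which these children differ, and the protocol itself makes it matter. The Background asks for more data "especially for children in the pre-myopia stag" (e), and Section 3.5.2 lists "the changes in the myopia incidence rate between the two groups" as a secondary outcome, to which only children not yet myopic can contribute.

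If refractive status is related to yearly elongation, an uneven split between arms moves the observed AL difference in this one trial. Nothing in the stated allocation limits that split, and nothing in the stated analysis removes its effect. At stake are some precision and the ease of defending the result if the baseline table shows an imbalance. An adjustment chosen only after seeing that table would be less convincing than one fixed beforehand.

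**Working it through.** **Inputs from the protocol.** Two-sided alpha 0.05, power 90%, SD 0.25 mm, effect 0.20 mm, 34 per group, 20% loss, at least 85 in total (Section 3.2.3); 86 in total, 43 per group (Section 1.2).

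**Assumptions, not in the protocol.** Pre-myopic share 30%, 50% or 70% (26, 43 or 60 of 86). Difference in yearly elongation between the types, g, of 0.05 to 0.20 mm.

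**Step 1: the plan's own figure.** A two-sample t-test with standardized effect 0.20/0.25 = 0.8 needs 33.83, so 34 per group. Allowing for loss, 68/0.8 = 85, or 34/0.8 = 42.5, rounded up to 43 per group = 86. Both stated totals reproduce. Power at 34 per group is 90.2%. The sample size is not in question.

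**Step 2: chance imbalance.** With 86 children split 43:43 and K of them pre-myopic, the number X in one arm is hypergeometric. The difference in shares is (2X − K)/43, with SD (2/43) × √[43 × (K/86) × (1 − K/86) × 43/85].

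| Pre-myopic of 86 | SD of difference | P(at least 10 points) | P(at least 20 points) |
|---|---|---|---|
| 43 | 10.8 points | 0.388 | 0.084 |
| 26 or 60 | 10.0 points | 0.240 | 0.034 |

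With 43 pre-myopic children, the smallest split that passes 20 points is 26 v 17, because 9/43 = 20.9 points.

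**Step 3: effect on the AL difference.** Shift = imbalance × g. For 20 points:
- g = 0.10: 0.20 × 0.10 = 0.02 mm, 10% of the planned effect.
- g = 0.20: 0.20 × 0.20 = 0.04 mm, 20% of the planned effect.

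The standard error at 34 per arm is 0.25 × √(2/34) = 0.061 mm, so these shifts are about one-third and two-thirds of a standard error. If the shift goes against the treatment, power conditional on that imbalance is 83% (effect 0.18 mm) or 74% (effect 0.16 mm).

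**Step 4: what adjustment gains.** If the SD of 0.25 mm already includes the variation between types in an even mix, the within-type SD is √(0.25² − g²/4).

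| g (mm) | Within-type SD (mm) | Power at 34 per arm |
|---|---|---|
| 0.05 | 0.2487 | 90.4% |
| 0.10 | 0.2449 | 91.3% |
| 0.20 | 0.2291 | 94.4% |

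The unadjusted figure is 90.2%.

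**Step 5: what stratification gains.** Permuted blocks of 4 (assumed size) within each category hold the arms to a difference of at most 2 children per category, 2/43 = about 5 points.

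**The case against.** The strongest reply is that nothing here is an error. Unstratified 1:1 randomization is valid, and chance imbalance is part of the sampling variation that the t-test's standard error already measures. The planning SD is stated for the two types together, so on its face the 90% power already allows for variation between them. All of this stands.

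A large imbalance is also unlikely, and about half of such imbalances would favour the treatment. The figures above fix the arms at 43:43. Independent coin flips give 32% to 33% for at least 10 points and 4.5% to 6.7% for at least 20 points, so the picture is similar. Section 3.3 does not exclude blocks either. It is silent on them, though blocks without strata would not balance refractive status.

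A reader might infer more than the protocol supports:
- *That refractive status decides the control condition.* Section 3 reads "allocation to intervention group (RLRL treatment) or control group (observe or wear single" vision glasses, but states no rule for which child gets which. The link is plausible and unwritten.
- *That refractive status decides progression.* Section 3.2.3 gives one pooled rate, so every value of g used here is an assumption.
- *That imbalance undermines a comparison among pre-myopic children alone.* With 34 evaluable pre-myopic children and a standardized effect of 0.8, power is 62% at 17 v 17 and still 59% at 21 v 13. The limit is the number of such children, not the balance, and the protocol plans no such AL test.
- *That uneven numbers at risk spoil the incidence comparison.* A split of 26 v 17 has an effective size of 2 × 26 × 17/43 = 20.6 per arm against 21.5 if even, a loss of about 4%.

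Finally, a statistical analysis plan that is not at hand may add a covariate. It could not change the allocation scheme, and the protocol does not leave the comparison open: it names an unadjusted one.

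**Conclusion.** The point holds as a modest improvement to a stated method. Neither allocation nor analysis uses a baseline variable that is already measured. A moderate imbalance of at least 10 points has a 24% to 39% chance and one of at least 20 points a 3% to 8% chance, for an assumed pre-myopic share of 30% to 70%. The larger imbalance would shift the AL difference by 0.02 to 0.04 mm if the types differ by an assumed 0.10 to 0.20 mm per year. On average, adjustment would raise power from 90.2% to between 90.4% and 94.4% for assumed gaps of 0.05 to 0.20 mm. If the types do not differ in elongation, there is almost nothing to gain for AL.

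The documents do not support reading this as bias, an invalid test, a wrong sample size or a likely bad split.

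**What to change.** In Section 5, replace the unadjusted t-test for 1-year AL change with a linear model (ANCOVA) containing arm and baseline refractive status, either as cycloplegic spherical equivalent or as pre-myopia v mild myopia. Choose one form in advance. The category needs a written cut-off, which Section 3.2.1 does not give. Report the AL effect within each category with a 95% confidence interval, as estimation only and without a claim of efficacy by category.

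In Section 3.3, if the list is not yet in use, generate it in permuted blocks stratified by the same category. The section says in the past tense that the table was generated, so this may be too late. If enrolment has begun, only the model change applies.

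The cost is one field at enrolment, a new computer list and slightly more analysis. The sample size does not change. If the statistical analysis plan already specifies such a model, Section 5 of the protocol need only be brought into line with it.

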### 178 **3.4 Study intervention and termination**

179 All intervention patients underwent RLRL therapy using a desktop red light therapy device  
180 (Eyerising, Suzhou Xuanjia Optoelectronics Technology, Jiangsu, China). After device  
181 dispensing, intervention patients were advised to complete treatment twice a day under their  
182 parents' supervision. Each treatment session lasted for 3 minutes, separated by at least 4  
183 hours. In the absence of adverse effects, patients were instructed to repeat the treatment on

184 five days per week. Treatment dates and times were recorded via the internet, allowing  
185 researchers to monitor participant adherence.

186 The power of the semiconductor laser output by this device as the light source for the eyes  
187 is 1.07mW, with a wavelength of 650nm. It has been detected as a Class 1 laser by the National  
188 Quality Supervision and Inspection Center for Photoelectric Product Optical Radiation Safety,  
189 meaning that it is safe for the eyes to be directly irradiated.

190 Model specification of the therapeutic instrument: RS - 200 - 2A

191 (1) Input power  $\leq 100\text{VA}$ , input voltage: AC10V - 240V, 50Hz/60Hz.

192 (2) Wavelength of the low-intensity single-wavelength red light:  $650\text{nm} \pm 10\text{nm}$ .

193 (3) Diameter of the low-intensity single-wavelength red light cursor:  $7\text{mm} \pm 3\text{mm}$ , and  
194 the light spot at the observation port is:  $10\text{mm} \pm 2\text{mm}$ .

195 (4) Light source output power:  $2.0\text{mW} \pm 0.5\text{mW}$ ; at a distance of 100mm from the light  
196 source, it is 1.07 - 1.42mW.

197 The intervention will be terminated when the subject experiences an unexpected serious  
198 adverse reaction (including a sharp decline in vision by more than two lines or a central  
199 scotoma in the visual field), the guardian or the participant requests to withdraw from the  
200 study, or for other reasons.

201

## 202 **3.5 Outcomes**

### 203 **3.5.1 Primary outcome**

204 The primary outcome is AL change from baseline at 1 year between the two groups.

### 205 **3.5.2 Second outcomes**

206 1) the changes of UCVA and BCVA

207 2) the changes of SER, SFCT and CCT

208 3) the changes in the myopia incidence rate between the two groups.

209

## 210 **3.6 Study procedures**

### 211 **3.6.1 Study visit schedule**

| Examination                                      | baseline | 1 months | 3 months | 6 months | 9 months | 12 months |
|--------------------------------------------------|----------|----------|----------|----------|----------|-----------|
| Education and machine distribution               | √        | –        | –        | –        | –        | –         |
| Informed consent                                 | √        | –        | –        | –        | –        | –         |
| UCVA                                             | √        | √        | √        | √        | √        | √         |
| BCVA                                             | √        | √        | √        | √        | √        | √         |
| Noncycloplegic refraction (objective/subjective) | √        | √        | √        | √        | √        | √         |
| cycloplegic refraction (objective/subjective)    | √        | –        | –        | √        | –        | √         |
| AL                                               | √        | √        | √        | √        | √        | √         |
| Slit lamp exam                                   | √        | √        | √        | √        | √        | √         |
| Intraocular pressure                             | √        | √        | √        | √        | √        | √         |
| fundus photography                               | √        | √        | √        | √        | √        | √         |
| optical coherence tomography (OCT)               | √        | √        | √        | √        | √        | √         |
| Advent events                                    | –        | √        | √        | √        | √        | √         |
| Machine recovery                                 | –        | –        | –        | –        | –        | √         |

212

### 213 3.6.2 Clinical examinations

#### 214 1) slit-lamp examinations

215 Carl Zeiss SL 115. To evaluate the eyelid, eyelashes, conjunctiva, cornea, anterior chamber,  
216 iris, pupil, lens, and anterior vitreous.

#### 217 2) Axial length

218 IOLMaster ocular biometer (Zeiss, Jena, Germany)

#### 219 3) IOP and CCT

220 NIDEK NT-530P Full Auto Tonometer (NIDEK, Tokyo, Japan).

#### 221 4) Computer optometry

222 NIDEK APK-1 autorefractor (NIDEK, Tokyo, Japan).  
223 5) Cycloplegic optometry  
224 compound tropicamide eye drops were applied to both eyes four times with a 10-minutes  
225 interval. After 40 minutes, refraction data were initially measured three times and  
226 averaged using the NIDEK APK-1 autorefractor, then confirmed by an optometrist using  
227 trial lenses.  
228 6) Fundus photography  
229 NIDEK, AFC-330 digital fundus camera (NIDEK, Tokyo, Japan)  
230 7) optical coherence tomography (OCT)  
231 NIDEK RS-300 SD-OCT (NIDEK, Tokyo, Japan)  
232

#### 233 **4. Data Collection and Management**

234 During the examination, paper-based inspection forms are used to confirm the completeness  
235 of the examination. After the baseline examination is completed, the data from the paper-  
236 based inspection forms is entered into the research database. The monitor reviews each  
237 original research record form to confirm that the clinical trial data is recorded in a timely,  
238 accurate, standardized, and complete manner. Finally, the data administrator from the  
239 statistical unit checks and enters the data.  
240

#### 241 **5. Statistical Analyses**

242 For each subject, data from the right eyes were utilized for analyses. Missing data were not  
243 imputed or replaced. The changes in ocular parameters were calculated as a difference  
244 between baseline and the respective follow-up values.

245 Statistical analysis includes statistical descriptions and statistical inference. Continuous  
246 variables were presented as means and standard deviations, while categorical data were  
247 presented by frequency and percentage. Group differences between the RLRL and control  
248 groups were assessed using t-test or ANOVA for continuous data and the Chi-square test for  
249 categorical data. Statistical significance was set at two-sided  $P < 0.05$ , and all analyses were  
250 performed using SPSS software version 21.0 (IBM., Chicago, IL).  
251

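### The 12-month axial length comparison uses completers only and leaves four earlier AL visits out of that contrast; a repeated-measures model would be a cheap protection against arm-dependent loss

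*Protocol*

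**What the plan says.** Protocol Section 3.5.1 sets the endpoint: "The primary outcome is AL change from baseline at 1 year between the two groups". Section 5 gives the analysis. It begins "For each subject, data from the right eyes were utilized for analyses. Missing data were not", and the sentence goes on to rule out imputation or replacement. Change is taken from baseline to each follow-up visit, and arms are compared by t-test or ANOVA.

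Four other places bear on this:

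- Section 3.2.3 sizes the trial after "adjusting for a 20% loss to follow-up".
- Section 3.3 says that the subjects and "the clinicians were not masked to the interventions. Other investigators, and the statistician" are treated differently: the first two know the allocation, the others are masked.
- Section 3.4 lists among the reasons for ending the intervention that "the guardian or the participant requests to withdraw from the" study.
- The visit schedule in Section 3.6.1 ticks AL at baseline and at 1, 3, 6, 9 and 12 months.

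Section 5 names no model that links the visits, no missing-data assumption and no sensitivity analysis for the primary endpoint.

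**The concern.** The missing-data rule and the test together make the primary result a complete-case comparison. A child last seen at month 9 contributes nothing to the 12-month contrast, although most of that child's growth over the year has been recorded.

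The setting makes selective loss credible. The control arm is observed or wears single-vision glasses, allocation is known, and AL is measured at every visit, so families may learn how fast the eye is growing (the Protocol does not say whether they are told). Parents of fast-growing controls might leave to seek other treatment. Parents of fast-growing treated children might leave because the device seems not to work. The first would shrink the estimated benefit and the second would inflate it.

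At stake is the primary effect estimate. The data that could correct for loss related to observed growth are already scheduled.

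**Working it through.** **1. The plan's own figure.** Inputs from Section 3.2.3: two-sided alpha 0.05, 90% power, control growth that "was approximately 0.40 mm per year (standard deviation [SD]: 0.25 mm) according to the" literature, and an expected effect given as "A 50% treatment effect was expected (reducing axial elongation by 0.20 mm").

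- Normal approximation: 2 × (1.960 + 1.282)² × 0.25² / 0.20² = 32.8, so 33 per arm.
- Noncentral t: 34 per arm (power 90.15%; 33 gives 89.3%).
- Loss: 68 / 0.8 = 85 in total; 34 / 0.8 = 42.5, so 43 per arm and 86 in total.

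The stated 34, 85 and 86 all reproduce.

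**2. What the inflation buys.** 43 × 0.8 = 34.4 completers per arm. The SE of the difference is 0.25 × √(2/34.4) = 0.060 mm, against 0.25 × √(2/43) = 0.054 mm with nobody lost. Power is about 90% against 95.6%. The inflation therefore covers the loss of numbers.

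**3. What it does not cover.** Within one arm, let d be the fraction lost and g the mean growth of leavers minus that of stayers. Since the overall mean is (1 − d) × stayers + d × leavers, the completer mean is off by −d × g. The between-arm difference is off by d times the difference in g between arms. If g is equal in both arms and so is d, the errors cancel. With d = 0.20 and an assumed g of 0.10-0.25 mm in one arm only, the bias is 0.02-0.05 mm, or 10-25% of the 0.20 mm effect. Opposite gaps in the two arms double this to 20-50%.

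**4. Simulation under assumed mechanisms.** 43 per arm, true difference 0.20 mm, 12-month SD about 0.24-0.255 mm, 20% loss per arm after month 6. Loss depends on AL growth seen at month 6, with the strength given as log-odds per SD. The correlations and mechanisms are assumptions; the Protocol gives none.

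| Who leaves | Completer difference (mm) | Error |
|---|---|---|
| At random, or same pattern in both arms | 0.199-0.201 | none |
| Fast growers, control arm only, log-odds 0.5 | 0.178-0.180 | 10-11% too small |
| Fast growers, control arm only, log-odds 1.0 | 0.160-0.163 | 18-20% too small |
| Fast growers, control arm only, log-odds 1.2 | 0.154-0.171 | 15-23% too small |
| Fast growers, red-light arm only | 0.237 | 18% too large |
| Fast growers from control and slow growers from red light | 0.124-0.125; 0.109-0.141 at log-odds 1.2 | 30-46% too small |

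The rows agree with step 3. An error of 0.200 − 0.163 = 0.037 mm implies g = 0.037 / 0.20 = 0.185 mm. Moving the same gap to the red-light arm gives 0.200 + 0.037 = 0.237 mm. Opposite gaps give 0.200 − 2 × 0.037 = 0.126 mm.

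In all these scenarios an estimator that uses the earlier AL values returned 0.198-0.202 mm. It does so because the simulated loss depends only on AL already observed.

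**5. Precision.** If loss is random and each leaver has an earlier value correlated ρ with month 12, the variance falls by a factor of about 1 − 0.20ρ². For ρ = 0.72 this is 0.896 (SE 5% smaller); for ρ = 0.98 it is 0.808 (SE 10% smaller). Where children may leave at any visit, so that less is recoverable, the simulated variance ratio was 1.06-1.14, an SE 3-6% smaller. Under growth-dependent loss it was 1.10-1.27, or 5-11%.

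**The case against.** The strongest reply is that bias is not shown, only possible. That stands. A reader might infer that a completer t-test is valid only when loss is unrelated to progression. This is too strong for a difference between arms: loss related to growth in the same way in both arms leaves the contrast unbiased, as steps 3 and 4 show. The Protocol also has features that favour retention. Section 7.1 offers controls free use of the device for 12 months after the trial, and exclusion criterion 12 removes families who cannot attend regularly. Neither rules out selective loss, and the first does nothing for loss in the red-light arm.

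Other inferences should also be resisted:

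- *Stopping the device means missing AL.* Section 3.4 ends the intervention and does not say that visits cease. Withdrawal from the study is what would remove data.
- *The earlier AL values are discarded.* Section 5 computes change at each follow-up visit, so they can be analysed at their own visits. They are unused only in the 12-month contrast.
- *ANOVA here means classical repeated-measures ANOVA with listwise deletion.* The term is not specified. If it were meant, the analysis would still be restricted to complete cases, so nothing is rescued.
- *The trial is underpowered because of missing data.* Step 2 shows that it is not, on its own assumptions.

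It can also be said that avoiding imputation is compatible with a likelihood model, and that a statistical analysis plan, not seen here, might specify one. The first is true; the difficulty is that rule combined with a t-test or ANOVA. On the second, the details of a model belong in such a plan and their absence here is no fault. But the Protocol itself fixes the rule and the test, so a different primary method would have to depart from its text.

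**Conclusion.** The point holds as a recommended improvement. The primary contrast is completer-only by the Protocol's own wording, 20% loss is planned for, and unmasked families make arm-dependent loss plausible. If it occurs at the assumed strengths in one arm, the 0.20 mm effect would be misestimated by about 10-23%, towards too small if fast growers leave the control arm and too large if they leave the red-light arm. Opposite selection in both arms would do more.

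Size and sign rest on assumed correlations, timing and mechanisms. A reader might infer that the trial is set up to favour the device, or that its primary result will be wrong. The documents support neither: they say nothing on who will leave or why, and matching loss patterns give no bias. The precision gain is real but modest, roughly 3-10% in SE under random loss, and would not justify the change alone. Since the stated 90% power is kept, this is not an essential correction. It is worth making because the remedy uses data already being collected.

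**What to change.** Amend Section 5 along these lines:

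> The primary analysis is a mixed model for repeated measures of AL change at 1, 3, 6, 9 and 12 months, in all randomised children with any post-baseline AL, analysed as allocated. Fixed effects are arm, visit, arm-by-visit and baseline AL by visit. The 12-month arm contrast is the primary result. One sensitivity analysis allows missing 12-month values to be missing not at random (for example, delta-adjusted). The completer t-test is supportive.

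The blanket rule against imputation should then be limited to the supportive analysis, since a delta-adjusted analysis usually imputes. The covariance structure and the range of delta can be left to the statistical analysis plan.

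The cost is wording and a little more analysis. No visits, children or change in sample size are needed. The model relies on data being missing at random given observed AL, which cannot be verified; the sensitivity analysis shows how far the result depends on it.
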